### Sample size

Based on a review of RCT results included in the 2015 Cochrane Review of group versus conventional antenatal care for women
^24^, we assume the intraclass correlation coefficient (ICC) between Arms 1 and 2 and Arms 3 and 4 will be no larger than 0.01. We assume the standard deviation of GA at delivery is no larger than 4.3 weeks under both intervention and control arms. At 5% significance, with 36 facilities, this trial is powered (80%) to detect a 0.5-week difference in GA at delivery with 214 observations (ANC and outcome) per facility. Assuming a follow-up rate of 70%, 306 women per facility will be required. Just over 11,000 women will be recruited and we expect to follow almost 8,000 mother-newborn dyads through the period of the six-week PNC visit. At an average rate of 23 eligible recruits per month per facility, the total study duration will be (a) 14 recruitment months (from the end of May 2017 to August 2018, (b) an additional six to seven months to observe the outcomes of the last cohort of women recruited (February 2019), and (c) three additional months to complete data processing and analysis (May 2019).

### Statistical analyses

To compare the study groups, socio-demographic and reproductive health characteristics, and health care facility descriptive bivariate analyses stratified by study arm will be conducted using Chi-square and Student’s t-test statistics for categorical and continuous data, respectively. Similar unadjusted bivariate analyses will be presented for the primary and secondary outcomes. Unadjusted, intention-to-treat generalized estimating equations (GEE) linear regression with robust variance estimation analyses will be conducted to assess the effectiveness of the treatment regimen on the primary outcome variable, gestation at delivery, and analogous linear and logistic analyses of will be conducted to assess continuous and categorical secondary outcomes (Model 1). For these outcomes, similar analyses will be conducted to control for design effect (Model 2) and the effects of any additional unforeseen differences in measured study group characteristics (Model 3). Model 3 will include all covariates that are statistically significant and judged as important differences between the study group (e.g. not simply significantly different due to large sample size) as identified by a backward stepwise Wald analysis (Model 3), which removes the covariate least associated with the outcome, and continues in that manner to remove covariates not significantly associated with the outcome at the α=0.05 level.

Model 1: Outcome=Independent Causal VariableModel 2: Outcome=Independent Causal Variable, adjusted for design effectModel 3: Outcome=Independent Causal Variable, adjusted for design effect plus (retained) covariates

Additionally, we propose comparing these methods with data-adaptive targeted maximum likelihood estimators (TMLE)
^25^. These would attempt to leverage the hierarchical structure of the data and would adjust for covariates through a data-adaptive algorithm. Multi-level analyses to adjust for facility-level characteristics will be considered.

The main analyses will compare the control group (Arms 1+2) with the intervention group (Arms 3+4). Subanalyses by study arm will be conducted.

Arm 1: Standard ANC/PNC careArm 2: Standard ANC/PNC care, with early pregnancy testing and ultrasoundArm 3: Group ANC/PNC onlyArm 4: Group ANC/PNC care, with early pregnancy testing and ultrasound

All descriptive and statistical analyses, including survey data, will be performed using SPSS for Windows version 23, Stata SE version 15.1 and R version 3.5
^26,
27^. Qualitative data from focus group discussions at nine and 18 months after implementation will be audio recorded, transcribed and translated from Kinyarwanda to English.. Transcripts will be organized into thematic areas with Atlas ti 7.5.18 using a content analysis approach.

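### Planned chi-square and t-tests of the outcomes make no allowance for facility clustering, and the model sequence leaves open whether Model 1 does

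*Protocol article*

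**What the plan says.** The Statistical analyses section of the protocol article opens with comparisons of the study groups: "descriptive bivariate analyses stratified by study arm will be conducted using Chi-square" and Student's t-tests, for socio-demographic, reproductive-health and facility characteristics. It then carries the approach over to the outcomes: "Similar unadjusted bivariate analyses will be presented for the primary and secondary outcomes". Clustering is not mentioned for either set of tests.

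The next sentence gives the assessment of effectiveness on gestational age to an unadjusted, intention-to-treat GEE linear regression with robust variance, with analogous linear and logistic models for the secondary outcomes (Model 1). After that, "similar analyses will be conducted to control for design effect (Model 2"), and Model 3 adds retained covariates. The cluster unit of the GEE is not given. The main analyses are defined only by their contrast, Arms 1+2 against Arms 3+4.

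The Study design section randomises health centers within matched pairs. The Sample size section allows for clustering: "we assume the intraclass correlation coefficient (ICC) between Arms 1 and 2 and Arms 3 and 4 will be no larger than 0.01", with 214 observations in each of 36 facilities.

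**The concern.** Chi-square and Student's t-tests assume independent observations. Women at one health center share providers, catchment area and allocation, and the plan itself allows a positive ICC. Tests on individual women would therefore understate the standard errors of the arm comparison and reject too often.

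The model sequence raises a related doubt. If Model 1 already clusters on facility, it is unclear what control for design effect at Model 2 adds. If it does not, the model said to assess effectiveness has the same weakness as the bivariate tests. With no model named as primary, an invalid p-value could stand in the report beside a valid one, with no rule for which governs.

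**Working it through.** **Inputs (Sample size and Study design sections).** 36 facilities, 18 per side of the main contrast; m = 214 observations per facility; ICC at most 0.01; SD at most 4.3 weeks; difference 0.5 week; power 80%; 5% significance, taken as two-sided because the text does not say.

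**Step 1: reproduce the plan's sample size.** "At 5% significance, with 36 facilities, this trial is powered (80%) to detect a 0.5-week difference in GA at delivery".
- Without clustering, n per arm = 2 × (4.3 × (1.960 + 0.842) / 0.5)² ≈ 1,161.
- With clustering, m = n(1 − ICC) / (k − n × ICC). Deducting one cluster per arm for the small number of clusters (k = 17) gives m = 1,161 × 0.99 / (17 − 11.61) = 213.2, rounded up to 214.
- A noncentral t calculation with 18 clusters per arm and 34 df also gives 214, with power 80.0%.
- 214 / 0.70 gives 306 recruited per facility, and 306 × 36 = 11,016.

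The stated figures therefore reproduce once clustering is allowed for. Analysed women number 36 × 214 = 7,704, against about 2 × 1,161 = 2,322 if they were independent.

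**Step 2: type I error of a test that ignores clustering.** Design effect DE = 1 + (m − 1) × ICC = 1 + 213 × 0.01 = 3.13. The standard error is too small by √3.13 = 1.77. Type I error = 2 × [1 − Φ(1.960 / √DE)] = 2 × [1 − Φ(1.108)] = 26.8%. The effective sample size is 7,704 / 3.13 ≈ 2,461.

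| ICC | DE (m = 214) | Type I error |
|---|---|---|
| 0.001 | 1.213 | 7.5% |
| 0.002 | 1.426 | 10.1% |
| 0.005 | 2.065 | 17.3% |
| 0.01 (plan's maximum) | 3.13 | 26.8% |

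Table 3 counts attendance and identification of high risk on all women who attended ANC 1. If that means about 306 per facility (an assumption), ICC 0.01 gives DE = 1 + 305 × 0.01 = 4.05 and 33.0%. The article gives no separate ICC for secondary outcomes.

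**Step 3: simulation.** With no treatment effect, 36 facilities of 214 women, ICC 0.01, no pairing and 4,000 runs, the rejection rates were:
- t-test on individual women: 26.4%
- t-test on the 36 facility means: 5.1%
- robust (sandwich) z-test clustered on facility: 6.7%

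**Step 4: which unit do the bivariate tests use?** The text does not say. Three points favour individual women. A chi-square test of a yes/no outcome counts women. Table 2 aggregates only gestational age by health center and compares the yes/no outcomes as rates or proportions across arms. The Statistical analyses section also warns of differences that are significant merely because the sample is large, a worry that fits thousands of women and not 36 facilities.

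**The case against.** The strongest reply is that the bivariate comparisons are only to be presented, while effectiveness is assessed by GEE with robust variance, a standard method for correlated data, and Models 2 and 3 are explicitly adjusted for design effect. This stands. A reader might infer that the trial's main answer carries a 27% false-positive rate. The article does not support that: clustered on facility, the GEE has about 5 to 7%. Nor does it say that Model 1 ignores clustering; it leaves the matter unclear.

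The individual-level reading is also an inference. The primary aim is set at cluster level and Table 2 aggregates gestational age by health center, so for that outcome a t-test on facility means is possible and would be sound. For the yes/no outcomes this defence is weak. T-tests on facility characteristics are unobjectionable.

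A reader might also infer that spurious baseline significance decides Model 3. The text requires covariates to be judged important as well, and retains them by backward Wald elimination on association with the outcome. The baseline tests may inform that model but are not its only route.

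The 27% is the value at the ICC's stated ceiling, and matching that removes between-facility variance from the contrast would lower it.

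Finally, the cluster unit of a GEE is often left to the analysis plan, and its absence alone would be no finding. What remains is in the article's own text: named tests that assume independence, applied to outcomes, and a sequence that places design effect after the model said to assess effectiveness.

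**Conclusion.** The concern holds for the bivariate outcome tests and, conditionally, for Model 1. Run on individual women, the t-tests and chi-square tests have a type I error of about 27% at ICC 0.01, 17% at 0.005 and 10% at 0.002. Nominal 95% intervals built the same way would cover about 73% of the time at the ceiling (100 − 26.8). These figures assume two-sided 5% tests, equal facilities of 214, no gain from pair matching, and the ICC assumed for gestational age. Model 1 shares the problem only if its GEE does not cluster on facility, which the wording leaves open. The main result is not shown to be wrong, but the article does not say which result is the main one.

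**What to change.** 1. Present outcomes and baseline characteristics by arm descriptively, or replace the chi-square and t-tests with versions that respect clustering, such as tests on facility-level summaries.
2. State that every model, Model 1 included, takes the facility or the matched pair as the independent unit, and say what Model 2 then adds or drop that step.
3. Designate one cluster-respecting model as primary. The Study status section says analysis is under way, so record when this choice was made.

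The cost is wording, a few lines of code, and wider intervals than the unclustered tests would give. No new data are needed.

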## Methods

### Study aims

The primary aim of this study is to evaluate the effect of group antenatal care on gestational age at birth, at a cluster level. The secondary aims of this study are to determine the effects of: group antenatal care, screening obstetric ultrasound, and urine pregnancy testing in the community on antenatal care attendance and women’s and providers’ experience of antenatal and postnatal care; group antenatal care on preterm birth rates; group antenatal care on mode of birth; and group antenatal care on the outcomes of neonates at 42 days after birth, specifically among preterm neonates.

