### Study design

The study is a pair-matched CRCT with four arms. In the five Rwandan districts selected for this study, we assessed 55 health centers to inform study design and site selection. First, we limited the data set to only those with an average of at least 48 first ANC per month, operating on the assumption that this would allow for formation of at least 2-4 ANC groups in the event the health center was allocated to the intervention. This gave us 50 potential health centers. We then limited to those that had more than one ANC provider during ANC days, which reduced the available health centers to 37. In total, 36 health centers (one was not matched to ensure pairing) were selected to participate in the study (see
*Extended data*: File 15)
^18^.

Next data on all other criteria for each health center was used to perform nonbipartite pair matching in R producing a list of strongest potential matches across all criteria. The study team then reviewed the possible matches and agreed on optimal pairings among facilities that had at least 2 ANC providers prioritizing matches with similar volume of ANC1 visits, and similar distance to the nearest district hospital. Within each pair, one facility was randomized to group ANC and PNC using a computer-generated random assignment and the other was randomized to continue delivering the standard models of focused ANC and PNC. Selected health centers were pair-matched based on 1) number of ANC providers, 2) ANC volume 3) delivery volume, 4) proportion of ANC1 before 16 weeks gestation, 5) baseline PTB rate, and 6) availability of key screening tests. Pairs were then further matched into quadruples by the study team based on ANC volume, where one pair within each quadruple was randomly assigned using a computer-generated random assignment to additionally implement basic obstetric ultrasound at the health center and early pregnancy testing at the community level and the other was not. No allocation concealment was used.

Therefore, each study facility has one of the four assignments as illustrated in

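### No stated model names the matched pairs or the ultrasound/pregnancy-testing factor used in randomisation, design effect is not a regression adjustment, and no model is named primary

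*Protocol article*

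**What the plan says.** Under Study design the trial is pair-matched: "Within each pair, one facility was randomized to group ANC and PNC using a computer-generated random assignment". The pairs were then grouped into quadruples, and "one pair within each quadruple was randomly assigned" to add ultrasound and community pregnancy testing. With 36 facilities this gives 18 pairs and 9 quadruples, and both members of a pair share the same ultrasound/testing status.

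Under Statistical analyses the primary outcome is handled thus: "Unadjusted, intention-to-treat generalized estimating equations (GEE) linear regression with robust variance estimation analyses will be conducted". This is Model 1, with the allocated care as its only term. Model 2 is written "Outcome=Independent Causal Variable, adjusted for design effect". Model 3 adds covariates retained by backward selection. TMLE is proposed for comparison, and multi-level analyses may be considered. The main contrast is Arms 1+2 against Arms 3+4. Pair, quadruple and ultrasound/testing status appear in no model, the GEE cluster unit is not given, and no analysis is ranked above the others.

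Under Sample size: "At 5% significance, with 36 facilities, this trial is powered (80%) to detect a 0.5-week difference in GA at delivery", with 214 observations per facility. Matching is not mentioned there.

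**The concern.** The article does not simply leave the model to a later document. It writes out three model statements, and none reflects how the facilities were allocated.

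If the GEE treats facilities as independent, variation shared by the two members of a pair stays in the standard error although it cancels from the treatment contrast. The same holds for any shift in recorded gestational age from ultrasound dating, because half the facilities on each side use ultrasound and half do not.

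Model 2 does not repair this. A design effect multiplies a variance; it is not a covariate. A GEE with robust variance already allows for clustering, so read literally Model 2 either repeats Model 1 or counts clustering twice.

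With Models 1 to 3 and TMLE all applied to one primary outcome and none designated, the headline estimate could be chosen after the results are known.

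**Working it through.** **Inputs from the article.** SD 4.3 weeks, ICC 0.01, m = 214 per facility, difference 0.5 week, 36 facilities, 5% significance (Sample size); 18 pairs, so 18 facilities per side (Study design). Sidedness is not stated; two-sided reproduces the plan's figure.

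**Assumptions, not in the article.** Correlation r between the mean gestational ages of paired facilities: 0, 0.1 or 0.3. Shift d in mean recorded gestational age at ultrasound/testing facilities: 0, 0.5 or 1 week.

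**1. The plan's own figure.**
- Variance of a facility mean: v = SD² × [ICC + (1 − ICC)/m] = 18.49 × 0.01 + 18.49 × 0.99/214 = 0.1849 + 0.0855 = 0.2704.
- SE of the difference, unmatched: √(2 × 0.2704/18) = 0.1733.
- Noncentral t on 34 df, effect 0.5: power 80.0%.

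The 214 therefore reproduces as an unmatched comparison of 18 with 18 facilities. A paired t-test (17 df) with no matching gain would need 263 per facility.

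**2. Effect of pairing.** The true variance of the difference is 2v(1 − r)/18, while an unpaired facility-level analysis keeps estimating 2v/18, an SE of 0.173. The true SE is 0.173, 0.164 and 0.145 at r = 0, 0.1 and 0.3. Simulated results with equal facility sizes:

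| r | Unpaired, t on 34 df: type I error | Unpaired power | Paired, t on 17 df: type I error | Paired power |
|---|---|---|---|---|
| 0 | 5.0% | 79.8% | about 5% | 77.5% |
| 0.1 | about 4% | 81.1% | about 5% | 81.6% |
| 0.3 | 2.1% | 84.1% | about 5% | 90.3% |

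**3. Effect of a dating shift (r = 0).** Ultrasound status is balanced across the two sides, so the shift cancels from the difference and the true SE stays 0.1733. The estimated facility variance rises by (d²/4) × (18/17).
- d = 0.5: 0.2704 + 0.0662 = 0.3366; estimated SE √(2 × 0.3366/18) = 0.1934. The test rejects beyond 2.032 × 0.1934 = 0.393; (0.5 − 0.393)/0.1733 = 0.617, so power is about 73%. Simulated type I error is 3.0%.
- d = 1: 0.2704 + 0.2647 = 0.5351; estimated SE 0.2438. The threshold is 0.4955; (0.5 − 0.4955)/0.1733 = 0.026, so power is about 51%.
- Paired test: about 77.5% in both cases, since pair members share ultrasound status.

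**4. Uncorrected robust z-test (r = 0, d = 0).** The plain sandwich variance is 17/18 of the unbiased one. P(|t34| > 1.96 × √(17/18)) = P(|t34| > 1.904) = 6.5%; simulation gives about 6.6%.

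**5. A repair to avoid.** With pair fixed effects and facility-level robust errors, each pair's residual is split equally between its two facilities. If SS is the sum of squared deviations of the 18 pair differences, the reported variance is SS/648, where the correct one is SS/(17 × 18) = SS/306. The SE is too small by √(306/648) = 0.687, and P(|t17| > 1.96 × 0.687) is about 20%.

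**The case against.** A reader might infer more than the article supports.

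- **That the unadjusted GEE is the lead analysis.** It is listed first but never labelled primary. What stands is that nothing is.
- **That it is certainly a facility-level analysis.** The cluster unit is not stated. If it were the pair, the robust variance would already reflect the matching. Facility is the likelier reading, because the sample size is unmatched, but it remains an inference.
- **That the matching is definitely ignored.** Adjusting for design effect may be loose wording for adding pair or quadruple terms, and TMLE is meant to use the data's hierarchy. The phrase is undefined, so neither reading can be confirmed.
- **That the trial falls short of its stated power.** It does not on the plan's own inputs: an unmatched analysis delivers the planned 80%, and the paired test gives slightly less. Power is lost relative to a paired analysis, and drops below 80% only if ultrasound/testing shifts recorded gestational age.
- **That false positives are inflated.** When pairing or dating matters, the error is mostly conservative. The 6.6% needs an uncorrected z reference that the article does not state, and small-sample corrections are commonly left to the SAP.
- **That the health-centre aggregation in Table 2 and the aim to "evaluate the effect of group antenatal care on gestational age at birth, at a cluster level" contradict a regression on individuals.** They need not: a GEE on women can estimate the effect of a facility-level allocation.

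The dating shift is also uncertain. The article plans to correct gestational age from postnatal measurements in every newborn, which could shrink it.

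**Conclusion.** The point holds as a mismatch between allocation and stated analysis, together with an undefined Model 2 and no designated primary model. That much follows from the text alone.

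The size is conditional. It requires a facility-clustered GEE and some effect of pairing or ultrasound dating on recorded gestational age, neither of which the article quantifies. Over the assumed range, unadjusted type I error runs from 5% down to about 2% with pairing. Power forgone against the paired test is about half a point at r = 0.1 and about 6 points at r = 0.3. A shift of 0.5 or 1 week puts unadjusted power at about 73% or 51%. If neither factor matters, the unpaired analysis is valid with a t reference and about 2 points stronger.

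The likely consequence is an interval that is too wide, and a result open to choice among models, more than a false claim of benefit. Should-fix.

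**What to change.** Name one primary analysis that follows the randomisation. Either of these would do:

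- a paired t-test (17 df) on the 18 within-pair differences in facility mean gestational age; or
- a GEE with variance clustered on the pair and a small-sample t reference.

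Both remove the ultrasound/testing effect, because it is common to the two members of each pair. Replace the design-effect wording of Model 2 with this specification. Do not combine pair fixed effects with facility-level robust errors. Keep Models 1 and 3 and TMLE as sensitivity analyses.

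The change is to wording only. Study status reports that analysis is already under way, so the choice should be recorded before results are reported. The downside is about 2 points of power (79.8% to 77.5%) if neither pairing nor dating explains any variance.

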## Abstract

**Background:** Group antenatal care has demonstrated promise as a service delivery model that may result in improved outcomes compared to standard antenatal care in socio-demographic populations at disparately high risk for poor perinatal outcomes. Intrigued by results from the United States showing lower preterm birth rates among high-risk women who participate in group antenatal care, partners working together as the Preterm Birth Initiative - Rwanda designed a trial to assess the impact of group antenatal care on gestational age at birth.

**Methods:** This study is a pair-matched cluster randomized controlled trial with four arms. Pairs randomized to group or standard care were further matched with other pairs into quadruples, within which one pair was assigned to implement basic obstetric ultrasound at the health center and early pregnancy testing at the community. At facilities randomized to group care, this will follow the opt-out model of service delivery and individual visits will always be available for those who need or prefer them. The primary outcome of interest is mean gestational age at birth among women who presented for antenatal care before 24 completed weeks of pregnancy and attended more than one antenatal care visit. Secondary outcomes of interest include attendance at antenatal and postnatal care, preterm birth rates, satisfaction of mothers and providers, and feasibility. A convenience sample of women will be recruited to participate in a longitudinal survey in which they will report such indicators as self-reported health-related behaviors and depressive symptoms. Providers will be surveyed about satisfaction and stress.

**Discussion:** This is the largest cluster randomized controlled trial of group antenatal and postnatal care ever conducted, and the first in a low- or middle-income country to examine the effect of this model on gestational age at birth.

**Trial registration:** This study is registered on ClinicalTrials.gov as
NCT03154177 May 16, 2017.

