We will also report several descriptive results of interest and identify factors that influence uptake, fidelity, and sustainability of group care in Rwanda. This includes the proportion of ANC and PNC visits at sites randomized to group care that occur in a group versus one-on-one with a provider. We will describe attendance at group care visits by men or female ‘next of kin’. Uptake will be measured by enrollment and mothers’ attendance at scheduled group antenatal care (gANC) visits. Furthermore, a subset of women will be included in a participant survey at enrollment (during pregnancy) and after birth; we will measure satisfaction with care, locus of control, perceived social support, perceived stress, and depressive symptoms (see
*Extended data*: File 3)
^18^. The postnatal questionnaire (unpiloted) will also include questions about health behaviors such as breastfeeding, post-partum family planning and use of an insecticide-treated bed net (see
*Extended data*: File 4 and 5)
^18^.

Additionally, providers at both group ANC and standard ANC study sites will participate in a longitudinal survey, with questionnaires administered at baseline, nine, and 18 months (see
*Extended data*: Files 6–8)
^18^. Measures of interest include level of education and years of clinical experience, job satisfaction and preferences, and perceived stress. We will report the uptake and effects of introducing urine pregnancy testing by CHWs and ultrasound by primary ANC providers.

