**ANC 1 within 1st trimester**	Women who attended ANC 1 <16 weeks	All women who attended ANC 1	ANC Register
**Identification of high risk**	Women with risk factors identified Number of women referred with risk factors	All women who attended ANC 1	ANC Register
**Maternal morbidity**	Cesaerean sections women referred for delivery women 'sick'	All deliveries	MAT Register, Referral Forms, RapidSMS

GA, gestational age; LMP, last menstrual period; MAT, maternity; NEO, neonatal; ANC, antenatal care; PNC, postnatal care;.

Other secondary outcomes will be measured. First, to survey a sub-set of participants across all trial arms, a convenience sample of the first five women to present for ANC per month are invited to participate in a baseline questionnaire measuring satisfaction with care, locus of control, perceived social support, perceived stress, and depressive symptoms. Similarly, among those who present at the health center with newborns approximately six weeks after birth, five women will be invited to participate in a follow-up questionnaire in which the same baseline questions are repeated and additional questions about postnatal health behaviors, including family planning uptake, insecticide-treated mosquito net use, and breastfeeding, are added
*.* This will be an unmatched cohort of survey participants and the baseline and postnatal questionnaires (see
*Extended data*: Files 3–5)
^18^. These questionnaires will be conducted in person by the data collector when the woman visits the health facility. Second, ANC and PNC providers in all arms are invited to participate in a longitudinal survey about job satisfaction, preferences, and perceived stress (baseline and follow-up questionnaires are available as
*Extended data*: Files 6–8)
^18^. These data will be collected at study training meetings or administered by data collectors at the facilities. The baseline data of providers trained to deliver group ANC/PNC will be linked to their longitudinal scores of group ANC model fidelity assessed at regular intervals by the Master Trainers (assessment tool appears as
*Extended data*: File 9)

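### The models for secondary outcomes do not pre-specify each provider's own baseline score, although the provider survey is longitudinal; the comparison is valid but less precise than it could be

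*Protocol article*

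**What the plan says.** The Outcomes section states that providers at both group and standard sites "will participate in a longitudinal survey, with questionnaires administered at baseline, nine, and 18 months", and lists "job satisfaction and preferences, and perceived stress" among the measures. Data collection confirms that "ANC and PNC providers in all arms are invited to participate in a longitudinal survey about job satisfaction, preferences, and perceived stress", in a paragraph that opens "Other secondary outcomes will be measured". The women's survey, by contrast, is described there as unmatched between its two rounds.

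The abstract's list of secondary outcomes includes "preterm birth rates, satisfaction of mothers and providers, and feasibility", and a secondary aim covers "women’s and providers’ experience of antenatal and postnatal care". Table 2, however, has no row for provider satisfaction or stress scores; providers appear there only under qualitative acceptability.

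Statistical analyses gives one generic sequence for secondary outcomes: "analogous linear and logistic analyses of will be conducted to assess continuous and categorical secondary outcomes (Model 1"). Model 1 is outcome on arm. Model 2 adds an adjustment for the design effect. Model 3 adds covariates that are significant and judged to differ importantly between groups, after backward Wald elimination at 0.05. A targeted maximum likelihood (TMLE) comparison with data-adaptive covariate choice is also proposed. None of these names the provider's baseline score, and no model combines the nine- and 18-month scores.

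**The concern.** A provider's baseline satisfaction or stress score is likely to be a strong predictor of the same score later. Under the stated sequence it is absent from Models 1 and 2. Its entry into Model 3 depends on between-group imbalance, which is the wrong criterion for a prognostic baseline. Under randomisation, a balanced baseline passes a valid 5% between-arm test about one time in 20, so a predictive score would usually be left out. If Model 3 is read instead as selecting on association with the outcome, entry still depends on the data. On neither reading is there a baseline-adjusted estimate fixed in advance.

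What is at stake is power. The number of providers is not stated, but the site criterion of more than one antenatal care (ANC) provider implies at least 36 × 2 = 72, against just over 11,000 women. A real effect on provider stress or satisfaction could be missed that the collected baselines would help to show.

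**Working it through.** **The plan's own figure.** The only stated sample size concerns gestational age: SD 4.3 weeks, difference 0.5 week, ICC 0.01, 36 facilities, 80% power, 5% significance. With two-sided t quantiles on 34 df (2.032 + 0.852 = 2.884), n per arm before clustering is 2 × (4.3 × 2.884/0.5)² ≈ 1,231. Then m = n(1 − ICC)/(18 − n × ICC) ≈ 214 per facility, as stated, and 214/0.70 ≈ 306. This does not bear on the provider survey, but it supports using t on 34 df below.

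**Inputs for the provider survey.**
- From the article: 36 facilities (18 v 18), more than one ANC provider per facility, and scores at baseline, nine and 18 months.
- Assumed, because the article gives no figures: 2, 3 or 4 providers per facility (72, 108 or 144 in all), ICC 0.05, correlation r = 0.3, 0.5 or 0.7 between any two occasions, true difference 0.5 SD. The same r is applied to facility means, and no provider is lost or lacks a baseline.

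**Variance ratio, baseline-adjusted to follow-up only.**
- One follow-up: 1 − r² = 0.91, 0.75, 0.51, a cut of 9%, 25%, 51%.
- Mean of two follow-ups: [(1 + r)/2 − r²]/[(1 + r)/2] = 0.56/0.65, 0.50/0.75, 0.36/0.85 = 0.86, 0.67, 0.42, a cut of 14%, 33%, 58%.

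**Worked example, 3 providers per facility.** Effective number per arm = 18 × 3/(1 + 2 × 0.05) = 49.1. SE unadjusted = √(2/49.1) = 0.202 SD. The detectable difference at 80% power is 2.884 × 0.202 = 0.58 SD. Multiplying by √(1 − r²) gives 0.56, 0.50 and 0.42 SD.

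**Power for 0.5 SD at one follow-up (noncentral t, 34 df).**

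| Providers | Unadjusted | r = 0.3 | r = 0.5 | r = 0.7 |
|---|---|---|---|---|
| 72 | 0.52 | 0.56 | 0.64 | 0.80 |
| 108 | 0.67 | 0.71 | 0.79 | 0.92 |
| 144 | 0.78 | 0.81 | 0.88 | 0.97 |

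**Validity.** In a simulation of 4,000 runs per setting (ICC 0.10, 3 providers per facility, r = 0.6), the type I error at one follow-up was 0.052 unadjusted and 0.046 adjusted. Both are close to 5%.

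**Sensitivity to the facility effect.** If facility effects are constant over time, facility means correlate more strongly than individual scores. With ICC 0.10, 3 providers and r = 0.6, the facility-mean correlation is (0.10 + 0.50/3)/(0.10 + 0.90/3) = 0.267/0.40 = 0.67. The gain would then exceed the simple 1 − r² figure. That assumption is favourable and cannot be checked from the article.

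**The case against.** The strongest objection is that the article never says explicitly that Models 1 to 3 apply to the provider survey. Table 2 omits these scores, survey data are mentioned in the analysis text only in the sentence on software, and covariates for a staff survey are often left to an analysis plan, which is not shown. This lowers the weight of the point. It does not remove it: the abstract and Data collection class the survey as secondary, and the article does fix a covariate rule for secondary outcomes.

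Four stronger readings are tempting, and the article does not support them.
- A reader might infer that the baseline score is shut out of every model. It is not: Model 3 or TMLE could admit it.
- A reader might infer that a chance baseline difference makes the unadjusted result misleading. The unadjusted test already allows for chance imbalance and holds its error rate.
- A reader might take the stated linkage of provider baseline data as proof that survey rounds can be matched. That linkage is to model-fidelity scores, and only for providers trained in group care.
- A reader might call the sample very small and the gain free. The provider number is not given. Questionnaires could be completed at study training meetings and allocation was not concealed, so some baselines may not be clean. Turnover may also reduce matched records.

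The magnitude rests wholly on assumed inputs. What stands is the efficiency loss alone.

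**Conclusion.** The point holds as a minor precision improvement. For a survey described as longitudinal and secondary, the stated models leave use of the provider's baseline score to imbalance, elimination or an algorithm. Fixing it in advance would cut the variance at one follow-up by about 9% to 51% for a correlation of 0.3 to 0.7. In the 108-provider example, power for 0.5 SD moves from about 0.67 to between 0.71 and 0.92. These figures assume complete, linkable baselines unaffected by allocation or training; losses would shrink the gain. No inference becomes invalid without the change, and neither the primary analysis nor any secondary outcome listed in Table 2 is affected.

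**What to change.** In Statistical analyses, add that for provider job satisfaction and perceived stress scores:
- the provider's own baseline score is a fixed covariate whatever its significance or imbalance, or a constrained longitudinal model with a common baseline mean across arms is used, which also keeps providers without a baseline;
- the nine- and 18-month scores enter one model with a time term, and clustering is by facility;
- the unadjusted comparison is reported as a sensitivity analysis.

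Use only baseline forms completed before group-care training, treating later ones as missing. Check whether the forms also preceded knowledge of allocation. Report by arm how many providers have a linkable, usable baseline.

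The cost is a few lines of analysis wording, one degree of freedom, and a provider identifier that links the three rounds, which the article does not confirm exists. Data collection ended on December 31, 2018, so an identifier not recorded then may not be recoverable. Some baselines may prove unusable or unlinkable, possibly more often in the group-care arms, which would reduce the gain. The wording should be settled before provider scores are compared by arm.
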